#### Sample size calculation

Expecting a 5 degree change in ankle ROM (assumed as clinically relevant), with a standard deviation of 4.5 degrees, a significance level (α) of 0.05 that is corrected for comparisons between three groups using a Bonferroni correction (α = 0.0167), and a power level of 80%, 13 children in each group will be sufficient. The calculation takes five repeated measurements with a correlation coefficient of ρ = 0.7 into account. In this study, 66 participants (22 in each group) will be recruited to allow drop outs.

#### Recruitment procedure

Subjects will be recruited from three centers: 1) the VU University medical center in the Netherlands (N = 18), 2) "Rehabilitation Medical Center (RMC) Groot Klimmendaal" in the Netherlands (N = 18) and 3) the Pediatric Neurology Cerebral Palsy Center at Washington University School of Medicine and St. Louis Children's Hospital in the USA (N = 30). Eligible subjects will be identified by the physicians during clinical sessions or from review of patient's charts. The recruited children and their parents will receive a letter about procedures and content of the study, as well as an informed consent form. The potential subjects and their caregivers will be informed by the site investigators and physicians. Both parents/guardians and children being 12 years old are asked to sign and return the informed consent to agree on voluntary participation in the study.

### Setting & design

A single blind randomized controlled trial will be performed at the three above mentioned centers. The participants will be assigned into 3 different groups. In addition to their regular treatment, two groups will be treated with a dynamic or static KAFO for one year to prevent for a reduction of ankle dorsiflexion at full knee extension and one group will be included as a control group without additional intervention. The morphological measurements will be performed only at Dutch participants at the VU University medical center.

Measurements will be performed at baseline and at 3, 6, 9 and 12 months after treatment allocation. In combination with those measurements, participants of the experimental groups will have a meeting with the orthotist and physician to check for complications with the KAFO.

The assessor and analyser are blinded for treatment allocation. The trial will be performed between January 2010 and December 2012.

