#### Secondary outcome - gait analysis

Sagittal and frontal video-recordings of the patient's gait pattern will be made at 50 Hz. The subjects will walk 5 times barefoot and 5 times with shoes and AFO if applicable, along a 10 m walkway at self-selected comfortable speed. Walking speed will be calculated from the time to complete a part of the track (5 meters, measured with infra red detectors or with a stopwatch, depending on measurement location). For follow up measurements, the patient will be requested to walk at baseline walking speed (within a range of ± 5%). Video recordings of the involved leg(s) will be taken in the sagittal and frontal plane. Three representative steps will be chosen for the assessment of the knee angle in midstance, the minimum knee angle in stance (between midstance and second bipedal phase of foot contact) and the ankle flexion in midstance. For the video analysis, a custom-made software package will be used (the Moxie Viewer^®^, VU University Medical Center, Amsterdam, the Netherlands, http://www.smalll.nl), and a software tool, allowing on screen video measurements of sagittal lower extremity joint angles [33]. For all participants, the gait related outcome measures will only be measured in the potentially treated legs.

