#### Premature termination of the study

The effects of orthotic management in rest on ankle dorsiflexion at full knee extension will be evaluated as soon as measurements have been performed on 30 children regarding follow-up measurement of 6 months. If the children in the control group show significantly larger *γ_(f-t) _*reduction compared to the other groups, this group will also be treated with a knee-ankle-foot orthosis. If the knee-ankle-foot orthoses groups (static and/or dynamic) show significantly larger reductions in *γ_(f-t) _*than the control group, the study will be terminated.

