### Blinding

The researchers performing the measurements and analysing the data will be blinded with respect to the treatment allocation. The children and their parents will be instructed to give no information about their treatment to the assessors. Blinding will be evaluated at the end of the study by asking the researchers the question: "In which group is the subject allocated and do you know this for sure, or is this a guess?"

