### Statistics

Statistical analysis will be performed according to an "intention to treat" principle. All relevant subject characteristics, such as age, body weight and length, gender, clinical diagnosis, will be described by their mean value and standard deviation, or percentages. Differences between groups at baseline will be tested using linear regression techniques or Chi-square statistics. The effect of the intervention will be analysed using a multi-level analysis, with the primary and secondary outcome measures as dependent variables and treatment group and time as independent variables. To test for any differences in the changes of variables between groups, a treatment*time interaction is included as independent variable. Analysis are adjusted for treatment site (Amsterdam, Arnhem or St Louis). Covariates will be: 1) KAFO wearing time, 2) lower leg growth, 3) use of an AFO by day, 4) stretching exercises and 5) level of spasticity. The α-value will be set at 0.05.

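### With KAFO wearing time in the stated model, whoever fits it can largely infer control versus KAFO, so the claim of a blinded analyser does not hold as written

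*Protocol article*

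**What the plan says.** The trial is single blind: families know their allocation, and masking rests on the people who measure and analyse. Setting & design says "The assessor and analyser are blinded for treatment allocation". The Blinding section says "The researchers performing the measurements and analysing the data will be blinded with respect to the treatment allocation". Neither statement is limited to a stage of the trial or to outcome scoring.

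The Statistics section specifies a multi-level model "with the primary and secondary outcome measures as dependent variables and treatment group and time as independent variables", plus their interaction and an adjustment for site. It then states "Covariates will be: 1) KAFO wearing time", followed by four further covariates. In Setting & design the comparison arm is described by "one group will be included as a control group without additional intervention", while under Intervention/comparisons the other two arms are asked for a minimum of six hours of wear each night.

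Premature termination of the study adds a comparison once 30 children have their 6-month measurement. One branch begins "If the children in the control group show significantly larger" and leads to KAFOs for the controls. The other branch, in which a KAFO group does worse than control, ends the study.

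**The concern.** The article claims a property (the data analyst does not know allocation) and also specifies an analysis that gives that analyst a variable tied to allocation. This is a conflict between two stated elements, so it is more than a detail left to another document.

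Assessor and analyser blinding is the only masking in this trial, and some outcome scoring calls for judgement. For gait, "Three representative steps will be chosen for the assessment of the knee angle in midstance". In the morphological part, the image plane and the target fascicle are selected on the reconstruction. If someone who makes such choices, or who settles the model, has seen wearing time first, the choices are no longer blind on the main contrast. The trial also could not accurately report that its data analysis was blinded.

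**Working it through.** The plan gives no figure on this point. The check compares sections and adds some simple counts.

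**Step 1: does wearing time reveal the group?**

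- The analysis file must hold a group variable, because treatment group and its interaction with time are in the model. Assume it is coded A, B, C.
- Under the stated model the file also holds wearing time. Controls are assigned no study KAFO, so their values should be zero or missing. The other two arms are asked for nightly wear.
- The code with essentially no wearing time is therefore the control group. With equal allocation that is 22 of 66 children, or 33%.
- Codes B and C both carry wearing time, and nothing in that variable says which is static and which is dynamic.

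For a single child the inference is weaker. A KAFO child who stops using the device stays in the analysis under Withdrawal and may also show zero or missing wear. The comparison across codes is what identifies the control group.

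**Step 2: does the interim rule reveal the group?**

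The two branches lead to different actions, so the rule cannot be applied without knowing which group is the control. The article does not say who runs the comparison or who applies the rule. A coded comparison decoded by a third person would satisfy the text. The rule therefore creates a risk and does not prove that the analyser is unblinded.

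**Step 3: are readings still outstanding at the interim?**

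Accrual is not stated, so even accrual is assumed. The trial window of January 2010 to December 2012 allows at most 24 months of entry before a 12-month follow-up. Planned follow-up visits are 66 × 4 = 264, of which 66 × 2 = 132 are at 9 and 12 months.

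- *24-month accrual.* Child i enters at 24i/66 months. Child 30 enters at 10.9 and is seen at 16.9. By then the 9-month visit is done for children entered by 7.9 months (21 children) and the 12-month visit for those entered by 4.9 months (13 children). Outstanding: (66 − 21) + (66 − 13) = 98 of 132, or 74%.
- *12-month accrual.* Child 30 enters at 5.45 and is seen at 11.45. The 9-month visit is done for 13 children and the 12-month visit for none. Outstanding: (66 − 13) + 66 = 119 of 132, or 90%.

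Most late readings would thus still be to come. Outstanding does not mean exposed, however. A reading is exposed only if the person who takes or scores it has learned the group, and the article does not establish that.

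**The case against.** The strongest reply is that analyser can mean two people. The conflict concerns whoever fits the regression; the harm to scoring concerns whoever reads video and ultrasound. Statistics names nobody, and no section makes these one person. If only the reader were meant, wearing time need never reach that person. Nothing says wearing time is merged before all readings are scored, a research assistant collects the diaries, and the interim section compares only the change in ankle angle, without mentioning covariates. A journal article may also leave group coding and data access to a fuller document.

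Much of this stands. It removes any claim that scoring will be biased, and any claim that the interim rule alone defeats blinding. It does not remove the core point, because the Blinding section covers those analysing the data without restriction, and the stated model gives that analyst wearing time. Unseen detail on coding would not help, since wearing time defeats the coding.

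Two stronger readings are tempting, and the documents support neither.

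- *The assessor is unblinded too.* Setting & design lists assessor and analyser as two roles, and naming them in one sentence under Blinding does not merge them. Knowing which group did worse at the interim would also not tell an assessor which child belongs to which group; labelled child-level data would be needed.
- *A fixed share of readings is exposed.* One could take the 30 interim children and quote 30/66 = 45% of 12-month readings and 30 × 2 = 60 of 264 visits, or 23%. This assumes that assessor and analyser are the same person and that no child is past 6 months, and it leaves out the other 36 children. Under the accrual assumptions above, the same 30 children would have 9 + 17 = 26 visits outstanding (10% of 264) with 24-month accrual, or 17 + 30 = 47 (18%) with 12-month accrual. The figure moves with the assumption, and the same-person premise has no support in any version.

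**Conclusion.** The point holds in a limited form. The statement that those analysing the data are blinded is not compatible with the stated model: whoever fits it can largely infer control versus KAFO, even with coded groups. That is the main contrast of the trial; static versus dynamic remains masked by this route. The conclusion assumes that controls accumulate little or no KAFO wear, as their assignment implies, and that the blinding claim covers the person fitting the model, as its wording does.

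The interim rule is a further risk whose size depends on who applies it, which the article does not say. Assessor blinding is not shown to fail, and no dependable percentage of affected readings can be given. The randomised comparison itself survives. What is at stake is the accuracy of the blinding claim and the protection of judgement-based scoring, so the plan should be changed, but the point is not fatal.

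**What to change.** 1. Score all outcomes, then fix and run the primary model, on a file with groups coded A/B/C and without wearing time, KAFO complaints or KAFO-related reasons for leaving the study.
2. Add wearing time only in analyses run after the code is broken, and limit the blinding claim in Setting & design and Blinding to the period before that point.
3. Run the interim comparison on coded groups without wearing time. Have the project-team member who generated the allocation sequence, whom the Randomization section already places outside recruitment and measurement, decode it against the existing rule. Pass no labelled or child-level result to assessors or scorers. This protects blinding only while neither branch is met, since the action that follows a met branch would be visible.

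The cost is protocol wording and some data handling, with no extra staff or children. The downside is that wearing-time analyses come slightly later and that wearing time leaves the blinded primary model. The latter is a real change to the stated model and should be recorded as one. The interim rule's content is untouched.

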### Intervention/comparisons

Patients of the control group will receive their usual care which may include ankle-foot-orthoses (AFOs) that are worn during the day (for standing and walking), oral baclofen therapy or other tone-reducing medications, strength training, stretching exercises, physical therapy, occupational therapy etc. Changes in usual care during the study will be monitored using questionnaires. Children will drop out of the study if they need surgical treatment (orthopaedic and neurosurgical procedures affecting muscle tone and length), botulinum toxin A injections in the lower extremity or serial casting treatments in the lower extremity.

In addition to their usual care, patients of the experimental groups will be treated for one year with a static KAFO or with a dynamic KAFO using an Ultraflex^® ^ankle power unit. Children will be asked to wear the KAFO at least 6 hours per night. They will be allowed to remove the KAFO during the night when the child is seriously uncomfortable after wearing the KAFO for at least 20 minutes or when the child wakes up at night with complaints concerning the KAFO. When children do not wear the KAFO for 6 hours per night, parents will be asked to increase wearing time by asking the child to wear the KAFO during rest activities in day time. In case of unilateral treatment, patients will sleep one night with and one night without a KAFO. In case of bilateral treatment, patients will wear a KAFO alternating on the right and left side each night.

#### Manufacturing the KAFO

The KAFO will be custom made by certified orthotists using polyethylene or polypropylene and foam (for a covered inside). Two transverse bars (polyethylene or polypropylene) above and below the knee will be used to reinforce and stiffen the KAFO. Bandages of nylon Velcro straps will be placed at three locations: 1) as high as possible on the thigh, 2) directly above the patella and 3) directly below the patella. A circular foot fixation, made of leather or soft polyethylene, will be used for foot fixation. This circular foot fixation will be closed with two velcro straps. One strap overlaps the patient's most convex part of the ankle and one strap will overlap the patient's foot proximal of the caput ossis metatarsal I and V. Deformity of the patient's foot will be corrected by the use of an internal three point pressure system (see Figure 2).

**Figure 2 F2:**
[figure not shown]
**Three point's pressure for correction of deformity**. (**a**)The equines correction will be performed by exerting force on the dorsal side of the lower leg (just below the knee), on the instep of the foot and under the ball of the foot. (**b**)The valgus correction of the calcaneus will be performed by a exerting a force laterally on the heel/calcaneus, laterally on the middle of the lower leg and medially on the lower leg, just above the medial malleolus. (**c**) The forefoot abduction correction will be performed by exerting a medial stabilization force calcaneus and talus and a lateral force on the calcaneus en the fifth os metatarsi. (**d**) The varus correction of the calcaneus will be performed by exerting force on the medial part of the calcaneus, medially on the middle of the lower leg and laterally on the lower leg, just above the lateral malleolus. (**e**)The forefoot adduction will be performed by exerting force on the tuberositas of the fifth os metatarsi, by exerting force laterally on the calcaneus and laterally on the first metatarsal phalangeal joint.

#### Static KAFO specification

The static KAFO will provide a fixed knee extension of 0° and a fixed ankle dorsiflexion angle of 0°.

#### Dynamic KAFO specification

The dynamic KAFO will also have a fixed knee extension of 0°, but will use an ultraflex^® ^ankle power unit (Ultraflex Systems, Pottstown, PA, USA). The force of the power unit that provides variable ankle dorsiflexion angles will be set according to the prescription shown in Figure 3.

**Figure 3 F3:**
[figure not shown]
**Manual for dynamic splint settings**.

### Outcome measures

#### Primary outcome

To measure the maximal ankle dorsiflexion angle at full knee extension, a Single Digital Inclinometer (Model ACU001, Acumar, Lafayette, IN, USA) will be used. This goniometer is attached to a torque wrench (Sensotork 713/6, Stahlwille, Germany). The goniometer-torque wrench combination is attached to an adjustable foot fixation. The foot fixation is constructed with a forefoot part and a calcaneal part. The two parts can be adjusted in rotation and in distance with respect to each other. With the adjustment in rotation, adjustments for fore foot adduction and supination can be made to stabilize instable valgus foot deformity. With the adjustment in distance, foot sizes can be accommodated from 150 to 240 mm. The calcaneal part has a heel support (width: 45 mm) and a point to attach the torque wrench. Both parts are equipped with Velcro straps for foot fixation [31]. Figure 4 shows a photograph of the measurement device attached to the foot. The ankle dorsiflexion angle will be measured as the angle between the footplate of the foot fixation and the tibia (*γ_(f-t)_*).

**Figure 4 F4:**
[figure not shown]
**Photographic illustration of the hand held dynamometer**. The hand held dynamometer consists of an adjustable foot fixation, a torque wrench and a goniometer. The foot fixation has parts supporting the forefoot and calcaneus. These parts are connected by a rod, allowing independent adjustments in rotation and abduction/adduction. The forefoot part is equipped with a fixation point to the table when needed (*).

The children will be asked to lie prone on a bench, with both feet overhanging the edge. The lower leg will lie in such a way that the fibula head and the lateral malleolus of the fibula are on the same height. The foot will be firmly attached to the adjustable foot plate for fixation. The ankle will be plantar flexed by the researcher, applying an external plantar flexion moment of 4 Nm, as measured using the toque wrench. The corresponding *γ_(f-t) _*is measured (further described as the 4 Nm plantar flexion angle). Subsequently, this procedure is repeated for 1 Nm plantar flexion and, 0 Nm, 1 Nm dorsiflexion, 4 Nm dorsiflexion and 6 Nm dorsiflexion. All measurements will be repeated six times and each moment will be exerted for five seconds. The *γ_(f-t) _*will be read out from the inclinometer simultaneously at the end of these 5 seconds at the target ankle joint moment. Positive values refer to an external dorsal flexion moment (Nm) of the dynamometer and dorsal flexion angle (°) of the ankle joint. There will be five seconds rest between each repetition and two minutes rest between each condition. The conditions will always be applied in the described order.

Children have to relax their muscles and will be asked to lie quietly during the measurements. Muscle activity will be checked using the electromyography (EMG) signals of *Tibialis anterior muscle *and *lateral Gastrocnemius Muscle*. The maximal voluntary muscle contraction (MVC) will be recorded before the measurements. The EMG signal will be A-D converted at 1000 Hz. After sampling, the signal will be high-pass filtered at 20 Hz to remove movement artefacts. Then, the signal will be normalized with respect to the MVC-value and filtered low pass at 5 Hz. EMG signals have to remain below 10% MVC during the angle and moment measurements to ensure muscle relaxation. Skin preparation and electrode placement of EMG will be carried out according to SENIAM guidelines [32].

The mean of the first 5 measurements for each condition in which the EMG signal remained below 10% MVC will be used for further analysis. The results will be used to create angle-moment plots in which, for example, the muscle tendon complex stiffness can be determined by calculating the slope of the line between the 0 Nm and 4 Nm (see Figure 5). A change in ankle dorsiflexion ROM will be investigated by analysing the *γ_(f-t) _*measured with 4 Nm dorsiflexion.

**Figure 5 F5:**
[figure not shown]
**Ankle-moment plots**. This figure will be created from the values measured with the hand held dynamometer. The dotted line will be used to calculate the muscle tendon complex (MTC) stiffness by calculating the slope of that line.

In case of potential bilateral treatment, the full procedure will only be performed on the participant's most involved leg. For the other leg, only the 4 Nm condition without EMG measurement will be performed to check for exit criteria (see withdrawal paragraph below). In case of potential unilateral treatment, the primary outcome measure will only be measured for the participant's potentially treated leg.

#### Secondary outcome - gait analysis

Sagittal and frontal video-recordings of the patient's gait pattern will be made at 50 Hz. The subjects will walk 5 times barefoot and 5 times with shoes and AFO if applicable, along a 10 m walkway at self-selected comfortable speed. Walking speed will be calculated from the time to complete a part of the track (5 meters, measured with infra red detectors or with a stopwatch, depending on measurement location). For follow up measurements, the patient will be requested to walk at baseline walking speed (within a range of ± 5%). Video recordings of the involved leg(s) will be taken in the sagittal and frontal plane. Three representative steps will be chosen for the assessment of the knee angle in midstance, the minimum knee angle in stance (between midstance and second bipedal phase of foot contact) and the ankle flexion in midstance. For the video analysis, a custom-made software package will be used (the Moxie Viewer^®^, VU University Medical Center, Amsterdam, the Netherlands, http://www.smalll.nl), and a software tool, allowing on screen video measurements of sagittal lower extremity joint angles [33]. For all participants, the gait related outcome measures will only be measured in the potentially treated legs.

